## Abstract

**Background:**

Antipsychotic trials in schizophrenia quantify treatment efficacy using clinician-rated scales such as the Positive and Negative Syndrome Scale (PANSS) and Brief Psychiatric Rating Scale (BPRS). If these scales include redundant or weakly informative items, measurement noise can blur drug-comparator differences that may dilute real effect sizes. Modern psychometric methods can refine and re-weight symptom scores that may improve precision and potentially increase detectable treatment effects, although it is unclear which approaches might be best.

**Aims:**

To 1) determine best psychometric models for the PANSS and BPRS, and 2) test whether psychometrically-informed scoring of PANSS/BPRS alters estimated antipsychotic effect sizes compared with conventional total-score analyses, and 3) to explore whether any changes differ across symptom domains and by sex.

**Method:**

We will conduct secondary analyses of anonymised individual participant data from randomized Phase II–IV schizophrenia trials accessed via secure data-sharing platforms (YODA Project and Vivli). Item-level PANSS/BPRS data will be harmonised at baseline and outcome. Psychometric models will be derived using confirmatory factor analysis, item response theory, and network analysis. Stability and invariance analyses will be conducted, examining covariates such as age and sex. Antipsychotic efficacy will be estimated using mixed-effects participant-level models, expressed as Cohen’s d standardised mean differences (SMDs) for both conventional and psychometrically-informed outcomes. The primary outcome will be the difference in SMDs between conventional and psychometrically-informed effect sizes, summarised across trials.

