Effect estimates from each model will be transformed into Cohen’s d to facilitate comparison across trials and scoring approaches. The primary effect of interest is the difference between SMDs derived from those derived from conventional scoring and psychometrically-informed outcomes (i.e. Model 1 vs Models 2a-c vs Model 3a-c, and Model 4 vs 5a-c vs Model 6a-c).

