### Trial-level analyses

In addition to pooled IPD analyses, treatment effects will be estimated separately within each trial using both conventional and psychometrically-informed outcome scores. For each trial, change from baseline to outcome will be modelled adjusting for baseline severity, and trial-specific SMDs will be calculated for both scoring approaches. The difference between the psychometrically informed SMD and the conventional SMD will be computed for each trial and treated as the trial-level effect of interest. Potential moderators (e.g. sex) may be explored descriptively or within mixed models where data permits.

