### Secondary analyses: Response

Secondary analyses will explore whether psychometric refinement meaningfully alters estimates binary outcomes such as response. Response will be defined using established PANSS or BPRS definition.
^
42–
44
^ Because binary outcomes may be sensitive to how thresholds map onto the underlying scale, these analyses will be treated as exploratory. The change in number of participants between psychometrically informed and original data will then be analysed using multilevel logistic regression models. Models will be fitted with and without adjustment for participant-level covariates.

Analyses will proceed in three steps:
1.Estimate baseline to outcome change in the proportion meeting response criteria within each arm, using both conventional and psychometrically-informed scoring.2.Estimate treatment and comparator differences in response using conventional scoring and psychometrically-informed scoring in separate models.3.Quantify the % difference between these two estimates (psychometrically-informed vs conventional) as the key comparison for secondary outcomes.

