In this context, psychometric re-modelling using pooled IPD may help clarify which symptom structures replicate reliably, which items contribute meaningfully, and whether abbreviated scales will capture the same responsiveness to treatment or whether weighted scoring yields more accurate estimates of change. Importantly, we do not claim that psychometric refinement necessarily produces clinically meaningful change at the individual level. Rather, the planned analysis evaluates whether relatively modest differences in effect size (e.g., ~10–15% as observed in prior IPD psychometric work) are detectable and may improve the precision, interpretability, or comparability of trial effect estimates. Yet, they can still matter for meta-analytic synthesis, trial power, and the likelihood of detecting true treatment differences under challenging conditions.

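### The primary outcome is an absolute difference in SMDs, but the size of change the protocol discusses is proportional, so contrasts between subgroups and trials can reflect the size of the drug effect rather than the benefit of the scoring

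*Protocol article*

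**What the plan says.** The protocol article fixes the primary quantity as a plain difference in three places. The abstract's Method paragraph says "The primary outcome will be the difference in SMDs between conventional and psychometrically-informed effect sizes, summarised across trials". Under Primary analyses: Continuous outcomes, for the pooled models, it says "The primary effect of interest is the difference between SMDs derived from those derived from conventional scoring and psychometrically-informed outcomes". Under Trial-level analyses it says "The difference between the psychometrically informed SMD and the conventional SMD will be computed for each trial", having first stated that "trial-specific SMDs will be calculated for both scoring approaches".

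The Discussion describes the size of change on another scale. The planned analysis is to evaluate whether "relatively modest differences in effect size (e.g., ~10–15% as observed in prior IPD psychometric work) are detectable". Under Secondary analyses: Response, the comparison is also worded as a percentage: "Quantify the % difference between these two estimates (psychometrically-informed vs conventional) as the key comparison for secondary outcomes".

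The reason for expecting any change is given in the abstract's Background, where "measurement noise can blur drug-comparator differences that may dilute real effect sizes". The main Background section likewise attributes the expected gain to less measurement error.

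The third objective asks whether changes differ by symptom domain and by sex. Exploratory subgroup and sensitivity analyses adds endpoint timing and stage of illness. No section links the SMD difference to the percentage.

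**The concern.** Under the noise-dilution rationale, better scoring raises each SMD by a common factor. The difference between two SMDs is then that proportional gain times the drug effect in the trial or subgroup concerned. Two subgroups in which the scoring helps equally will show different values of the primary quantity whenever their drug effects differ.

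This bears directly on the third objective. A larger difference in one sex, symptom domain, illness stage or endpoint week could be reported as a greater benefit of refinement when it only restates a larger drug effect. The summary across trials would likewise depend on the mix of drug effects in the repositories. The Limitations section itself expects effect sizes to be influenced by differences between trials. A pooled difference reported alone also cannot be set beside the 10–15% that the Discussion mentions.

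**Working it through.** **Inputs.** From the protocol: the primary quantity is a difference in SMDs; the illustrative size is 10–15%; the rationale is less measurement error. The protocol gives no target SMD difference, conventional SMD, reliability, between-trial spread or correlation between scorings, so there is no figure to reproduce. All such values below are assumptions.

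**Step 1: a proportional gain on the difference scale.** With conventional SMD d and gain g, the informed SMD is d × (1 + g), so difference = g × d.

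| Conventional SMD | 10% gain | 15% gain | A difference of 0.05 equals |
|---|---|---|---|
| 0.2 | 0.020 | 0.030 | 25% |
| 0.4 | 0.040 | 0.060 | 12.5% |
| 0.6 | 0.060 | 0.090 | 8.3% |
| 0.8 | 0.080 | 0.120 | 6.2% |

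For two subgroups with the same 10% gain: 0.10 × 0.25 = 0.025 and 0.10 × 0.50 = 0.050.

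**Step 2: why the rationale implies a ratio.** Under classical attenuation, observed d = true d × √reliability. If reliability rises from r0 to r1, the difference is true d × (√r1 − √r0), while the ratio is √(r1/r0) and does not involve the drug effect. With r0 = 0.70 and r1 = 0.85, the ratio is √(0.85/0.70) = 1.102 everywhere. The differences at true d of 0.3, 0.5 and 0.7 are 0.026, 0.043 and 0.060.

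**Step 3: spread across trials.** With a constant gain of 12.5% and a mean conventional SMD of 0.4, the mean difference is 0.125 × 0.4 = 0.05. A between-trial SD of the drug effect of 0.10 to 0.20 alone gives trial differences an SD of 0.125 × 0.10 = 0.0125 to 0.125 × 0.20 = 0.025, with no variation in scoring benefit.

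How visible this would be depends on sampling error. I simulated 25 trials of 400 participants with a constant 12% gain and mean SMD 0.42. A 5% homogeneity test on the differences rejected in the following shares of runs:

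| Correlation between scorings | Between-trial SD 0.10 | 0.15 | 0.20 |
|---|---|---|---|
| 0.97 | about 20% | 46% | 76% |
| 0.95 | about 13% | 28% | 51% |
| 0.90 | about 8% | 14% | 25% |

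The protocol article does not describe such a test. The rates only show how strongly the picture depends on the assumed correlation.

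**Step 4: is a ratio usable?** For single trials it is not. With 100 per arm, correlation 0.95 and a true gain of 12.5%, the simulated 95% range of the trial-level percentage change is −161% to +216% at d = 0.2, −10% to +64% at d = 0.4 and −2% to +36% at d = 0.6.

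Pooled, it is usable. Assume 10,000 participants in the placebo-controlled set, d = 0.42, ratio R = 1.12 and correlation ρ = 0.95. Then var(R) ≈ (4/N)/d² × (1 + R² − 2ρR) = (0.0004/0.1764) × (1 + 1.2544 − 2.128) = 0.002268 × 0.1264 = 0.000287, so the SE is 0.017. The 95% range is about 1.12 ± 0.033, or 1.09 to 1.15. This covers sampling of participants only; resampling trials as well may widen it.

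**The case against.** A reader might infer that the primary result cannot be compared with the 10–15% at all. The documents do not support that. Both SMDs are planned for every model and trial, so the percentage is one division away. What is absent is a stated conversion with an interval that respects the pairing of the two scores.

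A reader might also treat 10–15% as a decision threshold. It is Discussion wording, given as an example from earlier work, and no planned conclusion depends on it. The percentage comparison for response is weak support too: it concerns a binary outcome labelled exploratory, and could mean percentage points.

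The strongest objection is that the protocol never says the gain is multiplicative. The attenuation formula needs the same construct under both scorings, yet Models 2a–c drop items and Models 3a–c re-weight them, so the true effect may change as well. The Discussion also reports inconsistent shifts for some methods in earlier work. A ratio would then vary too. This stands: neither scale is free of the problem in every case, which is a reason to show both.

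It is also fair that an absolute difference is a legitimate estimand, and a more stable one where SMDs are near zero, as they may be in the any-comparator sensitivity analysis. Replacing it with a ratio is not justified. Finally, the sex, stage and timing analyses are labelled exploratory. That limits the harm, but comparison by symptom domain and sex is a stated objective.

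**Conclusion.** The mismatch of scales is in the current text and is worth correcting, but it does not make the primary outcome wrong. If the gain is proportional, as the measurement-error rationale suggests, equal scoring benefit gives differences that scale with the drug effect, by a factor of two between SMDs of 0.25 and 0.50. Subgroup contrasts and between-trial spread on the difference scale alone therefore cannot separate scoring benefit from size of drug effect.

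The conclusion rests on proportionality, which is an inference and not a statement of the protocol. The numerical illustrations rest on assumed SMDs, reliabilities, spreads and correlations. The point supports a companion measure, not a change of primary outcome.

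**What to change.** Keep the difference in SMDs as the primary and trial-level quantity. Then:

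- Under Primary analyses: Continuous outcomes and Trial-level analyses, add as a prespecified companion the ratio of the pooled psychometrically informed SMD to the pooled conventional SMD in the placebo-controlled set. Take its interval from resampling trials and participants, with each participant's two scores kept together.
- Report the contrasts by sex, symptom domain, stage of illness and endpoint timing on the ratio as well as on the difference.
- Show the trial-level differences against the conventional SMD before concluding that scoring benefit varies between trials or subgroups.
- Do not form the ratio for single trials or active-comparator contrasts, because it is unstable when the conventional SMD is near zero.

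The cost is plan wording and some resampling. Models, scores and data stay the same. It is best settled before results are seen.

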**Conclusions:**

This study will determine whether best practice psychometric refinement of existing measures meaningfully changes antipsychotic effect size estimates, informing outcome measurement choices and interpretation of trial results.

## Background

### Psychometric assessment and its relevance for estimating treatment effects in schizophrenia research

Multi-item psychometric scales are fundamental to clinical and psychiatric research and central to the assessment of symptom severity, treatment response and prognosis in schizophrenia. The Positive and Negative Syndrome Scale (PANSS
^
1
^) and the Brief Psychiatric Rating Scale (BPRS
^
2
^) are the most frequently used clinician-rated instruments to assess symptoms. Underpinning treatment guidelines and regulatory approval,
^
3
^ both scales are also widely used as primary outcome measures in randomised clinical trials (RCTs).

Over several decades, there has been substantial effort to evaluate the psychometric properties of both these instruments. In addition to approaches spanning classical test theory (e.g. confirmatory and exploratory factor analysis), more sophisticated statistical methods like Rasch-modelling and network analysis have been used in order to attempt to clarify the symptom structure, improve measurement precision or identify poorly performing items.
^
4–
8
^ This work has produced a large collection of evidence with differing or partially contradictory conclusions with respect to item functioning or scale structure and dimensionality. Most psychometric theories emphasise that validity is not an inherent property of an instrument, but rather that it depends on how well it measures the intended construct in a given population or context.
^
9,
10
^ Hence, when applied across different populations or interventions, continuous evaluation of psychometric scales using.
^
11,
12
^ However, it is not clear to what extent these continued psychometric refinements meaningfully improve conclusions drawn from studies using these instruments.

In principle, psychometrical optimization should increase statistical power by reducing measurement error, therefore, yielding more precise effect size.
^
13,
14
^ However, there is no consensus in the field that these expectations are empirically met, since a growing body of methodological literature shows that psychometrically refined scores are often.
^
15,
16
^ The claim of ‘improved measurement’ following psychometrical refinement therefore.
^
11
^ Current research in the field of depression has begun to fill this gap by linking psychometric analyses to the effect size estimation in randomised controlled trials (RCTs). Through combining individual participant data (IPD) from several RCTs, these investigations were able to compare treatment effects derived from psychometrically-informed models (from factor analytic, item response theory or network analysis models), to those with conventional total scoring. Results indicated that factor-analytical approaches could be increase estimated antidepressant treatment effects not universally improve outcome measurement the importance of careful interpretation of clinical relevance. Crucially, this emerging evidence reframes psychometrical optimization as a means to evaluate whether measurement choices substantially influence the estimation of treatment effects. From this perspective, it is no longer the question of how psychometric models best depict symptom structures, but whether conclusions drawn from such models meaningfully inform science, clinical practice or policy.

Despite continuous efforts in pharmacological development, reported effect sizes remain modest in schizophrenia trials.
^
16,
17
^ Although likely, it is still debatable whether shortcomings in the outcome measurements contribute to this pattern.
^
6
^ Despite extensive analysis of the psychometric properties of the PANSS and BPRS, no large-scale efforts have been made to assess whether psychometric refinements alter the estimated treatment effects in schizophrenia trials, nor whether such effects differ between demographic subgroups (e.g. sex) or symptom domains. This suggests the need for a systematic, large-scale assessment of psychometric approaches in schizophrenia research, explicitly examining their implications for effect size and outcome measurement.

The present protocol therefore describes how the EVIDENTIAL project
^
18
^ will address this gap in knowledge. This project will adopt similar methods to those described by Doyle and colleagues,
^
19
^ replicating and extending these to schizophrenia trials. The primary aim of the EVIDENTIAL project is to comprehensively examine the properties of the BPRS and PANSS to determine whether psychometric refinement might meaningfully alter schizophrenia symptom structure or performance, and more crucially, whether these changes might influence estimates of treatment efficacy examined in subsequent analyses. To achieve this, we have three objectives, corresponding to three research stages:
-To determine the best psychometric models for the PANSS and BPRS-To test whether psychometrically-informed scoring of PANSS/BPRS alters estimated antipsychotic effect sizes compared with conventional total score analyses-To explore whether any changes differ across symptom domains and by sex.

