### Outcome measures
*:* PANSS and BPRS

The PANSS
^
1
^ is one of the most widely used clinician-rated outcome measures in schizophrenia research. It comprises 30 items, each rated on a 7-point anchored severity scale (1 = absent to 7 = extreme), which is commonly summarised as three symptom groupings: Positive (7 items), Negative (7 items), and General Psychopathology (16 items), together forming a total score ranging from 30 to 210. Despite its extensive use, heterogeneity in reported factor solutions and item functioning has prompted concerns about the PANSS’ psychometric robustness and its sensitivity to treatment-related change under some conditions.
^
6
^
^,^
^
23
^

The BPRS is another long-established clinician-rated scale frequently used in psychopharmacology research to quantify a broad range of psychiatric symptoms (e.g., thought disturbance, affective symptoms, activation, hostility).
^
2,
24
^ We will utilize the BPRS version comprising 18 items, each rated on a 7-point severity scale (1 = not present to 7 = extremely severe), producing total scores that typically range from 18 to 126. As with PANSS, published work indicates that factor structures and item performance can vary across samples and settings, which is relevant when BPRS totals are used as trial outcomes.
^
7,
8,
25,
26
^

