### Statistical analysis plan

Analyses will be conducted within the secured environment of Vivli. Our approach will follow a two-stage workflow. First, we will use item-level PANSS and BPRS data to evaluate and select the best-fitting, state-of-the-art psychometric models of symptoms. Second, we will use the resulting psychometrically-informed scores to estimate antipsychotic treatment effects and compare these with effects derived from conventional PANSS/BPRS total scores, thereby quantifying whether and how psychometric modelling alters trial-level and pooled treatment effect estimates. We will follow a similar methodological approach as detailed in the publications provided by Doyle et al.,
^
19
^ regarding the exploratory and confirmatory factor analyses (EFA, CFA) and Byrne et al.,
^
11,
13,
15
^ regarding the item response theory framework (IRT) and network analytical approach (NA).

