### Stage 1: Establishing optimal psychometric models of PANSS and BPRS

### Exploratory and Factor analytic approaches

Data will be randomly split into exploratory and confirmatory datasets, as recommended by Lubke and Luningham,
^
27
^ with stratification by treatment group and trial to ensure balanced representation. For stratification and subsequent subgroup/invariance checks, active antipsychotic arms will be coded using literature-standard classification (primary approach: first-generation vs second-generation antipsychotics; where feasible, a third category for D2 partial agonists may be considered). In exploratory analyses, we will additionally code active agents using McCutcheon and colleagues’ data-driven receptor-based taxonomy,
^
21
^ namely muscarinic (M2-M5) receptor antagonists; dopamine (D2) partial agonists and adrenergic antagonists; serotonergic and dopaminergic antagonists; and dopaminergic antagonists. We will ascertain factor models of schizophrenia for baseline (pre-treatment), combined outcome (post-treatment; 6 weeks) and separately for placebo and treatment groups. We will further evaluate measurement invariance across major arm categories (e.g., placebo vs active treatment and, where supported, across active treatment-arm classes) within the best-fitting baseline model(s).

Parallel analysis will be applied to the exploratory datasets to determine symptom dimensionality.
^
28
^ Next, the EFA will be performed, using oblique rotation to allow for correlated symptom domains, to examine the factor structure of the exploratory dataset. Models will be refined iteratively by evaluating factor loadings below 0.3 and/or communalities below 0.4, with poorly performing items removed where justified to achieve stable and interpretable solutions.
^
29
^

In the confirmatory dataset, CFA will be used to formally test candidate psychometric models identified during the exploratory phase. In addition to simple structures derived from EFA, established alternative models, including higher-order and bifactor representations, will be evaluated.
^
30

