### Primary analyses: Continuous outcomes

For each instrument (PANSS and BPRS), outcome symptom severity will be modelled as a function of treatment assignment, adjusting for baseline symptom severity and accounting for clustering of participants within trials via random intercepts, as per best practice RCT modelling.
^
41
^ Detached from the psychometric modelling approach (CFA, IRT, NA) in Model 1 the overall effects of antipsychotics versus placebo, using conventional scoring (i.e., original raw scores) will be estimated. Model 2 comprises a set of related models that mirror Model 1, where raw scores are replaced with abbreviated sum scores based on the results of the psychometric analysis from stage 1. In Model 3 psychometrically-informed (weighted) scores, that are derived from the abbreviated models will be established. Model 2 and 3 will be calculated for each psychometric method separately (CFA, IRT, NA). Models 4, 5 and 6 will extend Models 1, 2a-c and 3a-c, by additionally adjusting for participant level covariates:
•Model 1 (conventional scoring): Outcome is the raw total score with treatment group and baseline score as covariates and a random intercept for trial.•Model 2 (abbreviated total scores): Outcome is a simplified total score created after removing redundant items (as per relevant psychometric method) treatment group and corresponding baseline abbreviated score included as a covariates and a random intercept for trial.oModel 2a – factor analysis abbreviated total scoreoModel 2b – IRT abbreviated total scoreoModel 2c – NA abbreviated total score•Model 3 (weighted psychometric scores): Outcome is a psychometrically derived score (e.g., factor score, IRT expected score, or net score) treatment group and corresponding baseline abbreviated score included as a covariates and a random intercept for trial.oModel 3a – factor analytic weighted scoresoModel 3b – IRT weighted scoresoModel 3c – NA weighted scores (net score)•Model 4: Model 1 additionally adjusting for participant-level covariates (e.g. sex, age [where available])•Model 5a-c: Model 2a-c additionally adjusting for the same participant-level covariates•Model 6a-c: Model 3a-c additionally adjusting for the same participant-level covariates

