### Exploratory subgroup and sensitivity analyses

Where feasible and supported by data availability, we will explore whether psychometric models and treatment effects vary by sex. Measurement invariance across sex will be assessed within the optimal psychometric models using established procedures. Where invariance is violated, group-specific psychometric models will be estimated, and primary and secondary analyses repeated using sex-specific scores.

To further examine the robustness of findings to potentially important sources of between-trial and clinical heterogeneity, we will attempt to conduct additional exploratory sensitivity analyses:
•Endpoint timing (week 4 vs week 6): Given that acute antipsychotic trials commonly report outcomes around week 6, but earlier endpoints (e.g., week 4) may yield different conclusions.
^
22
^ Therefore, we will, where endpoint timing can be harmonised and sample size allows, repeat analyses stratifying trials by the closest available acute endpoint (week 4 vs week 6).•Stage of illness: Where sufficiently detailed and harmonisable information is available, we will explore whether the best-fitting psychometric model(s), invariance results, and estimated treatment effects differ according to patients’ schizophrenia history (e.g., first-episode/early-phase versus multi-episode/chronic presentations, prior treatment exposure, or other trial-reported indicators of illness course).

These exploratory analyses are motivated by the clinical and methodological need to understand whether modelling choices or trial-design and population differences (such as endpoint timing or illness course) could materially influence inferences about treatment effects. All subgroup and sensitivity analyses will be clearly labelled exploratory, and interpretation will prioritise effect estimates and uncertainty, with transparent reporting of any constraints arising from limited sample sizes, inconsistent variable availability, or restricted harmonisability across trials, consistent with STROBE reporting principles.

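### Objective 3 asks about symptom domains, but no planned analysis addresses them, the total score is the only conventional comparator, and the score entering Model 3 is not fixed if several factors are retained

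*Protocol article*

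**What the plan says.** The Abstract and the Background both list three objectives. The second asks whether psychometric scoring "alters estimated antipsychotic effect sizes compared with conventional total score analyses". The third is "To explore whether any changes differ across symptom domains and by sex".

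Stage 1 leaves the number of dimensions open. The exploratory factor analysis is done "using oblique rotation to allow for correlated symptom domains", and higher-order and bifactor models are candidates in the confirmatory step. The Mokken and network sections also assess dimensionality.

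Stage 2 fixes the reference. The Statistical analysis plan section will take the treatment effects from the new scores and "compare these with effects derived from conventional PANSS/BPRS total scores". Model 1 reads: "Outcome is the raw total score with treatment group and baseline score as covariates and a random intercept for trial". Model 2 uses an abbreviated total for each psychometric method, and Model 3 a weighted score for each method. The primary effect of interest is the SMD difference between Model 1 and Models 2a-c and 3a-c, repeated with covariates as Model 4 against Models 5a-c and 6a-c.

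The Outcome measures section describes the conventional PANSS groupings, "Positive (7 items), Negative (7 items), and General Psychopathology (16 items", but no Stage 2 model uses them as an outcome.

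**The concern.** Two things are at stake. First, one half of a stated objective cannot be answered: whether the effect of re-scoring differs by domain needs a conventional and a psychometric score for the same domain, and the plan has no such pair.

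Second, the primary contrast is open to a choice that affects its meaning. A correlated-factor solution yields several scores. Depending on which one is carried forward, or how they are combined, the contrast with the total can change what is measured as well as how well it is measured. The article's motivation is noise reduction (Abstract, Background), so a reader will tend to take an SMD shift as a statement about precision. Where drug effects differ between domains, part or all of a shift could come from content.

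**Working it through.** **Step 1: trace the domain objective through the analyses.**

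- Models 1 to 6: raw total, abbreviated total or weighted score, with and without covariates. No subscale outcome.
- Trial-level analyses: the same scores within each trial; sex is the only moderator named.
- Response: conventional against psychometric scoring, no domain contrast.
- Exploratory section: "we will explore whether psychometric models and treatment effects vary by sex", then week 4 against week 6, then stage of illness. No domains.
- Table 1: the moderators are sex and stage of illness.

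So the sex half of objective 3 has an analysis and the domain half has none.

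**Step 2: trace the Stage 1 output into Stage 2.** Model 3 is introduced with a single score, while its sub-items 3a to 3c and the Stage 1 text use the plural. Neither says which score or scores enter the primary contrast if several factors are retained.

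**Step 3: how far can content alone move the SMD?** The article states no figure to reproduce. All inputs here are assumptions: domain SMDs of 0.50 (positive), 0.30 (negative) and 0.35 (general), domain SDs of 6, 6 and 10, and a common between-domain correlation r. Domain scores are taken as they stand, so nothing about measurement quality changes.

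Total SMD = sum(SMD × SD) / sqrt(variance of the total)

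- Numerator: 0.50×6 + 0.30×6 + 0.35×10 = 8.3
- Variance: 36 + 36 + 100 + 2r(36 + 60 + 60) = 172 + 312r

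| r | Variance | Total SMD | Positive vs total | Negative vs total | General vs total |
|---|---|---|---|---|---|
| 0.35 | 281.2 | 8.3/16.77 = 0.495 | +1% | −39% | −29% |
| 0.50 | 328.0 | 8.3/18.11 = 0.458 | +9% | −35% | −24% |
| 0.65 | 374.8 | 8.3/19.36 = 0.429 | +17% | −30% | −18% |

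In SMD units the positive-domain difference runs from 0.500 − 0.495 = +0.005 to 0.500 − 0.429 = +0.071.

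If all three domains had the same SMD, every domain score would still fall below the total, because the total aggregates. The ratio is sqrt(variance)/22: 16.77/22 = 0.76 (−24%) at r = 0.35 and 19.36/22 = 0.88 (−12%) at r = 0.65.

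**Step 4: abbreviated totals, which is what Model 2 specifies.** Assume 30 items of equal quality (7/7/16), with item correlation 0.35 within and 0.20 between domains. With w items kept per domain and per-item effect δ, SMD = sum(wδ) / sqrt(sum w + 0.35·sum w(w−1) + 0.20·sum over domain pairs of 2·w·w′).

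For δ in ratio 1.5 : 0.75 : 1:

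- Full scale: 31.75/sqrt(252.6) = 1.998 (arbitrary units)
- 7/5/8 items kept: 22.25/sqrt(113.7) = 2.087, or +4.5%
- 7/3/8 items kept: 20.75/sqrt(94.8) = 2.131, or +6.7%
- 5/7/8 items kept: −2.6%

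With a stronger ratio of 2 : 0.75 : 1, keeping 7/3/8 gives +12.3%. With equal per-item effects these three sets move by only −0.6% to −2.1%.

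**The case against.** A reader might infer that the plan sets a positive-symptom score against the total and will book the excess, about 10%, as psychometric gain. The documents do not support that. No section says a single-domain score enters the primary contrast. Model 2 is expressly an abbreviated total, and the Model 3 scores are derived from the abbreviated models. Objective 2 asks only whether scoring alters the effect size, and a total-score contrast answers that question as worded. Any single percentage rests on assumed inputs: the positive-domain shift is anywhere from +1% to +17% over the correlations tried, and the other two domains show losses. For abbreviated totals the movement stays below 10% unless the domain effects are assumed to differ strongly.

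It can also be said that this is a condensed article, that scoring principles are referred to cited depression publications, that Stage 1 promises a descriptive comparison of dropped items and loadings, and that objective 3 is exploratory. These points lower the weight of the concern but do not remove it. The article lists its exploratory analyses and omits one half of its own objective. It fixes the conventional comparator as the total in three places. The descriptive comparison would show a change of item content, but it would not give a domain-level effect contrast.

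The Background speaks of three research stages and the Statistical analysis plan section of a two-stage workflow. One might read this as a dropped domain stage; nothing in the text shows that, and the mismatch is editorial.

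**Conclusion.** The point holds in a limited form. From the text alone, the domain half of objective 3 has no planned analysis, the only conventional comparator is the total, and the score entering Model 3 under a multi-factor solution is not fixed. If a domain-specific or domain-weighted score is compared with the total, content and precision are mixed, and the shift can go in either direction.

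Its size cannot be settled from the documents. Under the stated assumptions, a positive-domain score differs from the total by about +1% to +17%, a negative-domain score by −30% to −39% and a general score by −18% to −29%. Abbreviated totals move less, from −2.6% to +12.3% in the cases shown. Content alone can therefore reach the 10 to 15% mentioned in the Discussion, but it need not. This should be changed before analysis; it does not show that the planned primary contrast is invalid.

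**What to change.** 1. For objective 3, add exploratory domain versions of Models 1 to 3. Compare each domain factor score or abbreviated domain score with the conventional subscale of closest item content: PANSS Positive, Negative or General, and a prespecified conventional grouping for the BPRS. Report the paired SMD difference per domain.
2. Prespecify which score enters Model 3 in the primary contrast when several factors are retained. Use an overall-severity score (general or higher-order factor, or an overall composite), so that like is compared with like.
3. Report the domain composition of every abbreviated or weighted score, and do not attribute an SMD shift to reduced noise where the domain mix has changed. This is needed even with step 2, because dropping or re-weighting items still alters the mix.
4. Align the wording on two or three stages.

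The cost is a few more exploratory models on item-level data already required, plus some wording. The main drawback is that the retained factors may map only imperfectly onto the conventional subscales; the mapping rule should be stated in advance and its limits reported.
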